**Figure 2 F2:**
[figure not shown]
Anticipated flow of participants through the study. Number of patients approached for screen, those who consented, and those who were assessed for eligibility will be recorded. Eligible patients will be invited to complete a baseline questionnaire (T0). After completion of the baseline questionnaire, participants will be randomised. Participants in the intervention arm will receive the intervention over 4–6 weeks. All participants will complete a follow-up questionnaire at 3 months postrandomisation (T1). Participants in the intervention arm will be invited to take part in a qualitative evaluation interview at the end of their involvement in the study. After completion of the follow-up questionnaire, participants in the control arm will receive the intervention materials.

### Randomisation, allocation concealment and blinding

Participants will be randomised in a 1:1 ratio to receive either the cognitive-behavioural therapy for renal fatigue (BReF) intervention or to the waiting-list control. Participants will be randomised at the individual level. Randomisation will be stratified by centre and randomly varying block sizes will be used to maintain balance of numbers in each arm across the period of recruitment while maintaining allocation concealment. King’s College London’s independent randomisation service will be used. Because the randomisation sequence is automated in real time, the allocation sequence is concealed from researchers. The trial coordinator will receive an automated email with the outcome of the randomisation procedure. The nature of the trial is such that blinding of participants cannot be achieved. Follow-up outcomes will be completed independently by participants by post or online. If baseline or follow-up questionnaires are not completed, then participants will receive reminder emails or phone calls and an assistance-based visit at the dialysis unit, by an independent researcher, who has not been involved in the intervention delivery. The statistician will remain blinded to treatment allocation.

### BReF intervention

The intervention is a tailored CBT-based self-management intervention with therapist support. The purpose of this intervention is to target individuals’ fatigue beliefs and behaviours in order to facilitate coping with renal fatigue (ReF). Further detail on the intervention can be found in figure 3. Therapist guidance was deemed necessary to facilitate engagement with the programme, particularly in the formulation of a personal biopsychosocial model of fatigue and identification of unhelpful thoughts and behaviours.^39–41^

**Figure 3 F3:**
[figure not shown]
Structure and content of the intervention. The intervention will follow a stepped approach over 4–6 weeks, accompanied by 3–5 sessions with a therapist. In level 1, participants will cover chapters 1, 2, a relevant chapter identified in the assessment and chapter 8. Level 2 focuses on cognitive therapy.

The development of the CBT-based intervention was systematic, based on the findings of reviews and qualitative and prospective studies, with substantial input from 10 patient and public representatives and a multidisciplinary team of health psychologists, clinical psychologists and nephrologists. The structure and content of the manual was drafted based on previous CBT interventions developed by one of our authors ([name]), such as ‘*Managing Your Multiple Sclerosis Fatigue: A Cognitive behavioural therapy manual*’ and ‘*Improving Distress in Dialysis*’^42–46^ and other sources.^47–49^

Participants will be provided with a structured CBT manual and a tasks workbook, including goal-setting sheets. This will be accompanied by three to five sessions with either a primary researcher who has a background in health psychology, basic CBT training and experience in working with fatigued patient groups (FP) or a registered health psychologist working in the renal setting (HC). In accordance with CBT principles, participants will be encouraged to complete tasks between sessions. Completion of these tasks has been found to be predictive of CBT outcomes.^50 51^

The manual consists of 10 chapters, accompanied by a tasks workbook for each session. Please see table 1 for the content of each chapter and associated tasks to be completed between sessions. The programme consists of two units, the basic unit (level 1) or the advanced unit (level 2). In the basic unit, participants will cover four chapters out of the manual, three will be accompanied by therapist sessions and one will be selected according to participants’ needs, established in the assessment. Participants, engaging well in the first two sessions, will be given the opportunity to cover an additional two chapters with the therapist over the phone (level 2). Engagement will be discussed in clinical supervision, and will be assessed through, for example, completion of between session tasks and focus maintained during the sessions. The brief and stepped structure of the intervention was chosen to meet patients’ needs, particularly their fatigability and potential concentration difficulties, according to the practical considerations previously raised with regards to the delivery of CBT in MS.^52^ Sessions will be guided by participants’ needs, identified through the self-monitoring tasks.

**Table 1 T1:** Summary of the content of the BReF manual

Chapter	Content	Between sessions task
ReF explained	Understanding ReF and alternative explanations A model for ReF Assessment of fatigue	Fatigue self-monitoring
Finding balance in activities and rest	Patterns of rest and activity and its effects on the body Planning activity and rest Exercise	Activity difficulty task Activity and rest goal sheet
Improving sleep	Sleep hygiene Maladaptive sleep patterns Improving sleep	Sleep, activity and rest goal sheet
Learning to relax	Diaphragmatic breathing Progressive Muscle Relaxation (PMR) Relaxation training: step-by-step	Relaxation diary
Coping with emotions	Strategies to cope with negative emotions Self-assessment of negative emotions Expressing emotions	Coping with negative emotions goal sheet
Managing stress	General tips to reduce the impact stress has on your life Managing controllable and uncontrollable stressors Mindfulness	Managing stress goal sheet
Making use of your social support	Creating a support network Disclosure versus keeping it to self Social comparisons	Social support goal sheet
Becoming aware of your thinking	Common unhelpful thoughts Identifying unhelpful thinking	Thought record
Changing your thinking	Identifying alternative thoughts	Alternative thoughts goal sheet
Preparing for the future	Sustaining and building on improvements Developing future goals Tips for everyday life	Long-term goals worksheet

BReF, cognitive-behavioural therapy for renal fatigue; PMR, progressive muscle relaxation; ReF, renal fatigue.

The first and last sessions will be face-to-face lasting 1 hour, while the remaining sessions will be over the phone, and will last 30 min. A combination of face-to-face and telephone sessions has been previously suggested for CBT in MS, to overcome possible limitations of individual delivery methods.^52^ Sessions will be scheduled at times that suit the participants. Face-to-face sessions will be conducted in a private environment. For the telephone sessions, participants will be encouraged to have the sessions in a quiet and private environment and allocate sufficient time not to feel rushed. Please see the Template for Intervention Description and Replication (TIDieR)checklist for a summary (table 2).

**Table 2 T2:** TIDieR checklist summary

Item 1: brief name	Item 2: rationale	Item 3: materials	Item 4: procedure	Item 5: who provided	Item 6: delivery mode	Item 7: location/setting	Item 8: when and how much	Item 9: tailoring	Item 10: how well (planned)
BReF	Please see the Introduction and intervention description (section BReF intervention)	BReF manual and tasks workbook	Please see sections: Flow of recruitment and participant timeline and BReF intervention	Primary researcher who has a background in health psychology and experience in working with fatigued patient groups or registered health psychologist working in the renal setting.	All sessions individual: −Two sessions face-to-face −One to three sessions over the phone	Recruitment from outpatient HD units in the UK. Therapy sessions in a private environment.	3–5 weekly sessions with the therapist, depending on engagement. Two sessions face-to-face, lasting 60 min. 1–3 sessions over the phone, lasting 30 min. 1 session completed independently.	Yes, tailored: optional session determined through the assessment in session 1. Tailored to participants’ needs, identified through the self-monitoring.	Therapists will follow a structured intervention manual. Therapy sessions will be audio-recorded and assessed for fidelity by the supervisor, [name].

BReF, cognitive-behavioural therapy for renal fatigue; HD, haemodialysis.

### Waiting-list control (control arm)

Participants allocated to the control arm of the study will receive their usual renal care, consisting of attending dialysis. As part of this feasibility trial, what constitutes usual care will be monitored to determine a control arm for a future efficacy trial and to handle potential contamination between the arms. After completion of the follow-up questionnaire, participants in the control group will receive the intervention manual and tasks workbook, but will not receive therapist support sessions. To minimise attrition from the control group, participants will be called to remind them that they can gain access to the programme in the weeks that follow.

### Clinical supervision

FP and HC will receive training on how to deliver the therapist support sessions from [name], with approximately 3–4 hours of face-to-face contact, in addition to audio-recorded role-playing sessions with feedback. FP and HC will receive continuous supervision throughout the intervention from [name], following the framework developed to support the delivery of psychological therapies with persistent physical conditions.^53^ This will involve reflection and discussion of the sessions, feedback on the audio-recorded sessions and case management, particularly following the initial session with each participant in terms of the treatment plan and subsequently discussions around each participant’s progress over the course of the intervention and progression to the level 2 sessions.

### Intervention fidelity

Two therapists will deliver all the intervention sessions following the detailed and structured manual developed for the patients. With permission from the participants, sought on the consent form, therapy sessions will be audio-recorded and a random sample assessed for fidelity during supervision by [name].

### Data collection and feasibility outcomes

The primary focus of this trial is the feasibility of the BReF intervention.

### Primary feasibility outcomes

Feasibility will be assessed by collecting descriptive data on recruitment and retention rates and willingness to be randomised according to Consolidated Standards of Reporting Trials feasibility and pilot trial guidelines.^54^ In the intervention arm, the degree of adherence to the intervention will also be assessed by recording completion of the chapter selected in session 1 and completed by participants independently in week 3 and the between sessions tasks, as well as recording of attendance at therapist sessions (ie, did not attend (DNA’s) and adherence to the assigned session time). Uptake of and adherence to the level 2 sessions will also be recorded. Given the exploratory nature of this trial, the number of completed intervention components will be assessed, this may help to identify an adherence cut-off for a future efficacy trial.

### Secondary self-reported patient outcomes

Self-reported patient outcomes will also be collected at baseline (T0) and 3 months postrandomisation (T1) via post or online. The assessment schedule completed by patients is summarised in table 3 and the self-report instruments used are described below.

**Table 3 T3:** Schedule of assessments

Assessment	Time		
	Screening	Baseline (T0)	Postintervention (T1)
CFQ	x	x	x
WSAS		x	x
PHQ-9		x	x
GAD-7		x	x
PSQI		x	x
BIPQ		x	x
CBSQ		x	x
SHI		x	x
IPAQ-short		x	x
CCI		x	
Sociodemographic characteristics	x	x	
Clinical characteristics	x	x	
Biochemical outcomes		x	x
Self-reported adverse events			x
Self-reported treatments for distress or fatigue during study			x
Qualitative interviews			x

BIPQ, Brief Illness Perceptions Questionnaire; CBSQ, Cognitive and Behavioural Responses to Symptoms Questionnaire; CCI, Charlson Comorbidity Index; CFQ, Chalder Fatigue Questionnaire; GAD-7, Generalised Anxiety Disorder-7; IPAQ-short, International Physical Activity Questionnaire -short form; PHQ-9, Patient Health Questionnaire-9; PSQI, Pittsburgh Sleep Quality Index; SHI, Sleep Hygiene Index; WSAS, Work and Social Adjustment Scale.

#### Fatigue severity

*Chalder Fatigue Questionnaire (CFQ)*^35^ measures fatigue severity via 11 items scored against a 4-point Likert-type response scale. Scores are assigned for each response, using continuous scoring from 0 to 3. A cut-off of >18 defines a fatigue case.^35 36^ Higher scores represent greater fatigue severity. The total score will be used here following recent psychometric evidence.^55 56^ This scale displays excellent psychometric properties^35 57^ and has been validated among patients on HD.^56^

#### Fatigue-related functional impairment

*Work and Social Adjustment Scale (WSAS)*^58^ consists of five items that correspond to impairment in work, home management, social activities, private leisure activities and relationships as consequence of an illness or symptom, in this case fatigue. Higher scores indicate greater impairment. It has good psychometric properties^58^ and has been previously used with patients on HD.^59^

#### Depression

*Patient Health Questionnaire-9 (PHQ-9)*^60^ measures depression over the last 2 weeks via a nine-item scale and an additional item to assess the impact of depression on functioning. Each item is scored from 0 (not at all) to 3 (nearly every day), with greater scores representing greater severity of depression. Depression severity cut-offs are available. The functional item is rated from ‘Not at all difficult’ to ‘Extremely difficult’. The PHQ-9 displays excellent psychometric properties and is responsive to change.^61 62^ The PHQ-9 has been validated in HD.^63^

#### Anxiety

*Generalised Anxiety Disorder-7 (GAD-7)*^64^ measures anxiety over 2 weeks, via a seven-item scale, and an additional item to assess the impact of anxiety on functioning. Each item is scored from 0 (not at all) to 3 (nearly every day), with greater scores representing greater severity of anxiety. Anxiety severity cut-offs are available. The functional item is rated from ‘Not at all difficult’ to ‘Extremely difficult’. The PHQ-9 displays excellent psychometric properties.^64 65^ This instrument has been used across chronic conditions, including HD patients.^42^

#### Sleep quality

*Pittsburgh Sleep Quality Index (PSQI)*^66^ measures seven components of sleep quality (subjective sleep quality, sleep latency, sleep duration, sleep efficiency, sleep disturbance, use of sleep medication and daytime dysfunction) over a 1 month time interval, via 19 items. Items are scored on an interval scale from 0 to 3. The scores of the components are then summed to obtain a global sleep quality score, ranging from 0 to 21. Higher scores indicate worse sleep quality. This scale displays satisfactory psychometric quality across patient populations^66 67^ and is widely used and has been validated.^68^

### Process variables

#### Fatigue perceptions

*Brief Illness Perceptions Questionnaire (BIPQ)*^69^ relies on a single-item approach to measure fatigue perceptions. It is a shorter version of the original Illness Perception Questionnaire (IPQ),^70^ with moderate to good associations between the two.^69^ Five of the items assess cognitive illness/symptom representations (consequences, timeline, personal control, treatment control and identity), two of them assess emotional representation (concern and emotions) and one item assesses illness/symptom comprehension. The items are rated using a response scale of 0–10. The psychometric properties of this measure have been assessed using samples from several illness groups, including renal disease,^69^ displaying satisfactory quality.

#### Cognitive and behavioural responses to fatigue

*Cognitive and Behavioural Responses to Symptoms Questionnaire (CBSQ)*^71^ includes five cognitive subscales; fear avoidance, embarrassment avoidance, catastrophising about symptoms, beliefs that symptoms signal damage to the body (damage beliefs) and symptom focus, scored from strongly disagree (0) to strongly agree (4). There are also two behavioural subscales; resting and avoidance of activity and all-or-nothing behaviour. All items are scored on a five-point frequency scale ranging from never (0) to all the time (4). Item scores are added from each subscale to obtain a total score. Across studies, this instrument displays acceptable psychometric quality^72^ and it has been used with different patient populations, including patients on HD.^59^

#### Sleep hygiene behaviours

*Sleep Hygiene Index (SHI)*.^73^ measures sleep-related behaviours via 13 items. Each item is rated on a five-point scale, ranging from 0 (never) to 4 (always). Total scores range from 0 to 52, with higher scores representing poorer sleep hygiene. This scale displays adequate reliability and validity.^73 74^ However, it has not yet been validated in kidney failure.

#### Physical activity

*International Physical Activity Questionnaire–short form (IPAQ-SF)*.^75^ measures self-reported weekly time spent on physical activities (walks, physical exertion of moderate and vigorous intensities) and inactivity (sitting) via seven items. The questionnaire can be scored categorically according to developed cut-offs to classify individuals into low, moderate or high physical activity groups; or it can be scored continuously. Responses can be converted to metabolic equivalent task minutes per week (METmin/week), according to the IPAQ scoring protocol. MET scores across the three subcomponents can be summed to indicate overall physical activity.^75^ The IPAQ is the most widely validated questionnaire, however, with some inconsistent evidence on its reliability and validity.^76^ Given its brevity, simplicity and extensive use across research, it was selected here to measure physical activity.

### Adverse events

Information about occurrence of serious adverse events since the start of the study will be collected by self-report postintervention, according to good clinical practice guidelines. Adverse events will be flagged up to the trial management team and participants will be contacted to further assess the adverse event and its relationship to the study.

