### Objectives

A feasibility design was deemed necessary to determine whether a full-scale randomised controlled trial (RCT) is feasible, by considering numbers meeting eligibility criteria, rates of recruitment and retention postrandomisation, floor/ceiling effects that might affect sensitivity to change; as well as by identifying any intervention-specific issues, particularly occurrence of adverse events and timing burden. The following aims will be addressed in this feasibility RCT:Objective 1: to estimate rates of recruitment and retention.Objective 2: to estimate willingness to be randomised.Objective 3: to explore the level of adherence to the intervention (intervention arm only).Objective 4: to estimate the standard deviation (SD) of fatigue in this patient population in order to compute a more robust estimate of the sample size required for an efficacy trial.Objective 5: to preliminary assess the psychometric properties of the self-report instruments used.Objective 6: to explore the potential benefits of the intervention at reducing fatigue severity and fatigue-related functional impairment as compared with the waiting-list control.Objective 7: to explore the potential benefits of the intervention at reducing depression and anxiety and improving sleep quality as compared with the waiting-list control.Objective 8: to examine change in fatigue-related cognitions and behaviours, and whether their effect differs between the intervention and control arm.Objective 9: to qualitatively explore patient perceptions of the acceptability and usefulness of the intervention and identify areas of improvement for a future full-scale trial.Objective 10: to explore any intervention-specific issues, particularly setting, mode of delivery of the intervention and acceptable number of sessions/chapters.

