Given the feasibility nature of the trial, statistical significance will not be assessed; instead effect sizes and CI will be estimated. An analysis of covariance (ANCOVA) will be performed to estimate the postintervention mean difference in outcomes, controlling for the baseline levels of each outcome, for the following variables: fatigue severity, fatigue-related functional impairment, depression, anxiety and subjective sleep quality, thereby addressing objectives 6 and 7. Group allocation will be included as an indicator variable following the intention-to-treat principle. Recruitment centre will also be controlled for in the analysis as it is a stratification factor. Differences in intervention effects by sociodemographic and clinical factors on fatigue outcomes will be explored.

Changes in fatigue perceptions, and cognitions and behaviours in response to fatigue will be evaluated via ANCOVAs to address objective 8. The proportion of the treatment effect that may be accounted for by these process variables with CI will also be calculated, as there will be insufficient power for mediation analyses.

To meet objective 9 and qualitatively explore the acceptability and usefulness of the intervention from the perspective of the participants, the semistructured qualitative interviews will be transcribed verbatim and analysed using inductive thematic analysis with the use of NVivo software. Thematic analysis revolves around identifying recurrent themes and patterns from the interviews and developing a coding manual.^87^

To address objective 10, a mixed methods approach will be used, drawing on both the quantitative and qualitative findings to determine any intervention-specific issues, such as the optimal number of sessions.

Considering issues relating to recruitment and retention rates, suitability of the selected measures, as well as any intervention-specific issues, will help us to determine whether to proceed to a full-scale efficacy trial, if so, these findings will also inform aspects of the design of the efficacy trial, such as the required sample size and appropriate self-report measures to ensure sufficient power and sensitivity to detect any intervention effects.

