### Ethics

The trial is co-sponsored by King’s College London and King’s College Hospital NHS Foundation Trust. Patient consent will be obtained. The Chief Investigator (CI) and all members of the research team will preserve the confidentiality of participants taking part in the study and will work in accordance with the Caldicott Principles, Data Protection Act 1998, NHS Code of Confidentiality and any relevant NHS Trust organisational policies. All serious adverse events related to the study will be reported to the study sponsor, ethics committee and relevant NHS R&D departments. Authorisation will be sought from the study sponsor for any future substantial and non-substantial amendments arising during the course of the study, prior to submission to the HRA. The study may be subject to inspection and audit by King’s College London under their remit as sponsor and other regulatory bodies to ensure adherence to GCP and the NHS Research Governance Framework for Health and Social Care (second edition).

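### The article defines the scope of adverse-event collection in two ways, and the narrower one would leave non-serious events without systematic recording in either arm

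*Protocol article*

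**What the plan says.** Five places in the protocol article bear on the scope of adverse events.

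- **Objectives, opening paragraph.** One reason given for a feasibility design is "identifying any intervention-specific issues, particularly occurrence of adverse events and timing burden". There is no limit to serious events.
- **Table 3, schedule of assessments.** The row reads "Self-reported adverse events" and is marked at T1 only. Again there is no limit.
- **Adverse events, first sentence.** "Information about occurrence of serious adverse events since the start of the study will be collected by self-report postintervention". This is the only sentence that defines what is collected.
- **Adverse events, second sentence.** "Adverse events will be flagged up to the trial management team and participants will be contacted to further assess the adverse event", with an assessment of whether the event is related to the study. The word 'serious' is gone.
- **Ethics.** "All serious adverse events related to the study will be reported to the study sponsor", as well as to the ethics committee and the R&D departments. This concerns onward reporting.

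The Analysis plan says that Objective 10 will be addressed by "drawing on both the quantitative and qualitative findings to determine any intervention-specific issues". It also lists intervention-specific issues among the matters that inform the decision whether to proceed to a full-scale trial.

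**The concern.** Two people could build the T1 questionnaire from this article and produce different forms. One who starts from the first sentence of the Adverse events section would ask about serious events. One who starts from Table 3 would ask about adverse events of any grade. The resulting data differ.

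The difference matters because the article itself singles out the occurrence of adverse events as a reason for running a feasibility trial. The intervention consists of therapist sessions and tasks on activity and rest, sleep, relaxation, emotions and thinking (Table 1). It is reasonable to expect, though the article does not say so, that many problems with such tasks would not meet a seriousness criterion. On a form limited to serious events, those problems would have no place to be written down in either arm. An absence of reported related events could then be taken for an absence of problems. Table 3 schedules the item once, so the information could not be collected afresh at a later visit.

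**Working it through.** The article states no figure on this point, so there is none to reproduce. The check is a comparison of wording.

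| Place | Function | Scope as worded |
|---|---|---|
| Objectives, opening paragraph | Purpose of the design | Adverse events, unrestricted |
| Table 3 | Schedule at T1 | Adverse events, unrestricted |
| Adverse events, sentence 1 | Collection | Serious adverse events |
| Adverse events, sentence 2 | Handling and assessment | Adverse events, unrestricted |
| Ethics | Onward reporting | Serious and study-related events |

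1. The Ethics sentence does not conflict with the others. A trial can collect all adverse events and pass on only those that are serious and related.
2. Of the remaining four, three are unrestricted and one is restricted. The restricted one is the sentence that defines collection, so a majority count does not settle the matter.
3. The second sentence of the Adverse events section cannot widen the scope in practice. An event can be flagged and assessed only if the form first captured it.
4. Other sources cover part of the gap:
   - **Scales.** CFQ, PSQI, PHQ-9 and GAD-7 are completed at T0 and T1 in both arms, so worsening of fatigue, sleep and mood is measured. The Analysis plan uses these outcomes through baseline-adjusted mean differences, and a mean can improve while some individuals get worse. Problems outside these domains are not covered.
   - **Interviews.** At least 10 are planned, in a subgroup of the intervention arm. With 40 participants randomised 1:1, that arm has 40/2 = 20. Interviews may reveal problems, but they give neither a count for the arm nor a comparison with control.

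**Illustration only.** With the article's assumed 80% retention, the intervention arm returns 20 × 0.80 = 16 T1 forms. The chance of at least one affected participant among n is 1 − (1 − p)^n. The rates p below are assumptions; the article gives none.

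- Related serious events, p = 1%: 1 − 0.99^16 = 0.15.
- Non-serious events, p = 10%: 1 − 0.90^16 = 0.81.
- Non-serious events, p = 20%: 1 − 0.80^16 = 0.97.

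Under these assumed rates, a form limited to serious events would probably return no related event, even if non-serious events were common enough that an unrestricted form would probably show some. This shows why the choice of scope matters. It is not an estimate for this trial, and it applies only if the form follows the restrictive sentence.

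**The case against.** The strongest reply is that this is one stray word. The article nowhere says that only serious events are collected. The next sentence, the schedule and the rationale all point the other way, and the actual T1 form may well ask about every adverse event. That stands as far as it goes: the documents do not show that non-serious events are excluded. They show that the scope is stated inconsistently.

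A second reply is that worsening fatigue, sleep or mood is already measured in both arms by validated scales, and that interviews and clinical supervision give further routes for problems to surface. This also stands in part. It would be wrong to say that such a participant leaves no trace in the data. What is missing is a record of the event, an assessment of its relation to the study, and a count that can be compared between arms.

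A reader might infer more than the text supports on three points.

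- **That the trial cannot answer a tolerability question of its own.** The article does not pose the question in those terms, and the sources above provide some information.
- **That adverse events were dropped from Objective 10.** That objective is worded "to explore any intervention-specific issues, particularly setting, mode of delivery of the intervention and acceptable number of sessions/chapters". The list gives examples and is not closed, and nothing shows that adverse events once stood in it.
- **That the lack of an adverse-event summary in the Analysis plan is an error.** Such a table may sit in a statistical analysis plan that is not shown, and an article commonly leaves it there.

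**Conclusion.** The point holds as an internal contradiction about scope. The sentence that defines collection is narrower than the stated purpose, the schedule and the sentence that follows it. If the T1 form follows that sentence, the purpose of identifying the occurrence of adverse events is met for serious events alone, and non-serious events are neither systematically recorded nor compared between arms.

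The size is modest. No sample size, estimate or confidence interval is affected, and the existing scales and interviews soften the loss. It is more than a clerical slip because the form's content depends on it and the item is asked once. The conclusion rests on the published wording; the T1 questionnaire itself is not shown and may already be unrestricted. In that case only the text needs correcting.

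**What to change.** 1. Reconcile the first sentence of the Adverse events section with the second sentence, Table 3 and the Objectives. State that the T1 item, given to both arms, collects adverse events and that each is marked serious or not. The Ethics rule on onward reporting can stay as it is.
2. From data already collected, report by arm the number of participants whose CFQ, PHQ-9 or GAD-7 score worsened from T0 to T1. Higher scores are worse on all three. Fix in advance what counts as worsening (any increase, or a stated threshold). For CFQ, read the counts as a comparison between arms: everyone enters above the cut-off, so scores may drift down in both arms regardless of treatment.

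The cost is a change to one questionnaire item, a short amendment and a small descriptive table. The downside is slightly more burden for fatigued participants and some minor, unrelated events to list and assess.
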